#### Hypothesis

Individuals who receive the **MI**^**2 **^intervention will show significantly more movement in PAPM stage at 120 days post randomization than those receiving a general breast cancer prevention health education intervention (**C**).

## Methods/Design

### Study 1: Development - Formative Research

This study is a randomized intervention testing the efficacy of a novel intervention program for increasing breast cancer screening use among rural minority women. The study employs a partnership intervention between Community Health Workers and Latina and American Indian women to provide breast cancer education and promote the use of an 'implementation intentions-based' approach for breast cancer screening (See Table 1: Implementation Plan). Eligible (i.e., 40 years of age or older and not up-to-date on breast cancer screening), consenting participants will complete a baseline computerized Healthy Living Kansas-Breast Health (HLK-BH) assessment while attending one of many community or church-based events scheduled within their respective home community. The HLK-BH program will gather data on past breast cancer screening behavior, breast cancer screening barriers, perceived breast cancer susceptibility and screening self-efficacy. Consenting age-eligible, not up-to-date participants will be randomized to a mammography "implementation intentions" intervention arm (**MI**^**2**^) or a control (**C**) arm (described in detail below). Participants will be enrolled from well attended community events scheduled on an annual basis in and around Mayetta in northeast Kansas (to capture the American Indian population) and Garden City in southeast Kansas (an area highly populated with Latinos). Details regarding site selection, randomization, intervention methods, sample size calculations, and data analysis procedures are described below. We project that 121 women 40+ years old and not up-to-date with mammography screening will be required for each of the study arms to detect the proposed intervention effects.

**Table 1 T1:** Implementation Plan

Study	Tasks	Year
**Study 1**: Development and Formative Research	Refine computer program, refine assessments (e.g., HLK-Breast Health, 120-day post randomization telephone follow-up), convene community advisory board, pilot test full HLK-Breast Health computer program.	1 - 2

**Study 2**: Randomized Trial	Finalize recruitment procedures, implement HLK-Breast Health program and 120-day post randomization telephone follow-up, perform preliminary data cleaning and initial data analysis.	3 - 5

**Study 3**: Data Analysis and Dissemination	Complete data cleaning, data analysis, project-related manuscripts, and follow-up grant development.	4 - 5

#### Design

This study will be a randomized trial that will evaluate the differential impact of the **MI**^**2 **^(intervention) and **C **(control) study arms on 120-day post randomization breast cancer screening utilization rates. Randomization will occur at the participant level. Women will be randomized to a treatment group within each community outreach recruitment event. This stratified random sampling design will minimize the variation between the **MI**^**2 **^and **C **intervention arms by allocating the variation between each Northeast and Southwest Kansas recruitment event to the strata parameters. In doing so, the variation between interventions will be minimized, much like a randomized complete block design.

#### Healthy Living Kansas-Breast Health Computer Program Development

##### Computer Program

Notebook computer will be used to conduct the Healthy Living Kansas-Breast Health (HLK-BH) program. Notebook software interfaces will be programmed by personnel from the University of Kansas (KU) Design for Health group - a network of communications, information technology, and web design professionals that have collaborated with our Healthy Living Kansas research team over the past several years. We anticipate that the HLK-BH program will be conducted on an electronic computer platform but will ask Latina and American Indian community members to decide whether they would prefer an Internet-enabled or notebook PC-based program (where data are saved on the computer and not uploaded to the Internet). For individuals reticent with completing the HLK-BH program via any electronic format, we will have a paper and pencil version available as well. The KU Design for Health staff will utilize their graphic design and effective communication campaign knowledge to ensure that the final HLK-BH product has a crisp, user-friendly look to it while still being easily navigable. With the input of community members, we will work to make the program culturally sensitive by having two programs with identical data elements but one tailored to Latinas and the other tailored to American Indian women. Each program will also be enhanced with clickable voice and video clips in English and Spanish to assist participants with lower literacy levels. Program team members will work to achieve a notebook product that has high literary contrast, readable font type and functional font size with an overall presentation that is complete with compatible non-glaring hues and tones.

##### Healthy Living Kansas Breast Health Assessment (HLK-BH)

Study investigators have collaborated to develop a comprehensive cancer assessment for use in our current Healthy Living project. The breast cancer questions contained in the previously developed cancer assessment will provide the platform from which the research team will develop the HLK-BH program for the notebook computers used in the proposed study.

#### HLK-BH Part I

Part I of the HLK-BH program will begin by screening for eligible study participants. Eligible participants will be 40-74 years of age and not up-to-date on breast cancer screening as defined by the American Cancer Society. Persons who are 40-74 years of age or older but who report being up-to-date on breast cancer screening will receive a one-page on-screen summary report that indicates they are up-to-date on breast cancer screening and reinforces their healthy breast behavior. Persons deemed eligible (i.e., meet age and breast cancer screening criteria) will continue with Part II of the HLK-BH program.

#### HLK-BH Part II

Part II of the HLK-BH program will begin with an on-screen consent procedure. The research team currently uses an on-screen consent procedure in our Healthy Living project (described in the Preliminary Studies section). If a participant does not consent to the study, she will immediately receive an on-screen summary report that promotes breast cancer screening, and describes why being up-to-date with breast cancer screening is important. Consenting participants proceed with answering questions about breast cancer screening awareness, breast cancer testing preferences, breast cancer screening barriers, perceived breast cancer susceptibility, screening self-efficacy, and breast cancer risk status. Demographic questions will assess marital status, employment status, years of education, income, race, and ethnicity.

Whenever possible, HLK-BH questions will be adapted from already existing and validated questions from widely used surveys (e.g., Behavioral Risk Factor Surveillance System Survey, National Health Interview Survey). Members of the Community Advisory Boards will review all components of the HLK-BH and notebook computer presentation to identify ways in which it may be improved. Previous studies conducted by the research team using computer tablets and tablets in primary care practices revealed the importance of keeping assessments brief. The research team will strive to restrict the assessment to 10-20 minutes. All HLK-BH questions will be subjected to computer readability analyses. We will use computer software developed by Readability Calculations that assesses text readability using nine recognized formulae [52].

The full HLK-BH tablet program will be pilot tested with community members to ensure that the program length is manageable and is running smoothly. Persons who participate in the HLK-BH notebook computer pilot will not participate in the proposed randomized trial. The research team will work with the advisory boards and community members to develop additional methods to assure assessment brevity.

#### Community Health Worker Training

CHWs will be trained and meet compliance criteria prior to recruiting study participants. Training elements will include: 1) reviewing the implementation intentions protocol manual, 2) reading a training workbook with a series of publications and reviews of breast cancer screening guidelines, breast cancer screening intervention studies, implementation intentions theory, and Health Education theory, 3) participating in training sessions conducted by study investigators, 4) conducting simulated recruitment intervention sessions, with sessions recorded and supervised by the P.I., 5) participating in follow-up training sessions conducted by study investigators, and 7) participating in ongoing evaluation by the P.I..

Training content will include the theoretical models and key principles underlying implementation intentions and the intervention overview. In addition, the study P.I. will train CHWs to respond to participant concerns regarding breast cancer screening and interaction with the health care system (e.g., exam initiation, procedural details, follow-up). CHWs will be trained to educate participants about approaching their physician or ancillary staff to request a mammogram referral, how to address concerns with exam procedures and, when to refer participants to their physician for questions and concerns related to breast cancer screening. To ensure CHWs are adequately trained, they will conduct practice sessions with each other, with volunteer participants, and with pilot participants prior to recruiting participants for the study. These sessions will be videotaped and the P.I. and Project Director will conduct supervisory sessions to provide guidance and feedback to the CHWs.

For purposes of CHW training and ensuring fidelity to principles and protocols of the implementation intentions, we will use a rating form adapted from our recent Healthy Living Kansas colon cancer screening study. Adherence to CHW principles will be rated on a 1-7 (Poor/Never to Excellent/Always) scale. Scores of 4 or higher represent adherence at the level of "good" or "often". Acceptable performance will be indicated by a mean score of 5 or higher with no score on any criterion being below 3. CHWs will have to achieve acceptable performance across all criteria on three consecutive practice participants before being permitted to recruit participants. If performance drops below the threshold (i.e., a mean of five and a minimum of three on all criteria), additional supervision will be conducted. Each of the CHWs subsequent sessions will then be supervised until three consecutive tapes again meet the threshold.

### Study 2. Randomized Trial

#### Participant Eligibility

Eligibility criteria for randomized trial participation include: individuals must be 40 years of age or older and not up-to-date with breast cancer screening as defined by current American Cancer Society recommendations (see Table 2). Individuals with an acute medical illness or a history of breast cancer will be excluded from the study. Although no formal assessment of dementia or psychiatric illness will be performed, participants demonstrating impaired cognitive function or inappropriate affect or behavior will be excluded from the study. Individuals with another household member enrolled in the study also will be ineligible. Individuals who have been enrolled in the study will not be eligible for repeat enrollment. This is true even if greater than one year has passed since their initial participation. Anyone not eligible for the study but interested in breast cancer screening and information will be given printed self-help materials (*What you need to know about Breast Cancer*, National Cancer Institute, *Breast Cancer and You*, Centers for Disease Control). Participants must have a current, active mailing address and access to a functioning telephone to ensure that the 120 day telephone follow up can be completed.

**Table 2 T2:** Participant Eligibility

Inclusion Criteria	Exclusion Criteria
• Latina or AI/AN woman residing in one of participating communities • Aged ≥40 years of age • Not up to date on mammography screening • Home address & access to a working telephone • Responded to 120-day post randomization follow-up call	• Receipt of mammogram within past year • Acute medical illness, history of breast cancer • Cognitive impairment or inappropriate affect or behavior • Another household member enrolled in the study

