#### CHW/Participant Partnership Implementation Intentions (MI^**2**^) Intervention

Each participant in the **MI**^**2 **^intervention arm will receive brief one-on-one breast cancer screening education delivered in person by a CHW. Following the education information delivery, the CHW will guide participants through the Healthy Living Kansas-Breast Health computerized screening and intervention program. This program will guide participants through a screening/eligibility assessment and implementation intentions protocol via automated computerized algorithms. If, upon screening, a person is deemed eligible to participate in the randomized trial (e.g., they are eligible for but not up to date on breast cancer screening), the computer program will automatically and immediately assign them to either the intervention or control arm. The total time required per participant to complete the education session and HLK-BH notebook computer program will be kept to a maximum of 20 minutes.

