#### 120-Day Post Randomization Follow-Up

All **MI**^**2 **^and **C **participants will receive a follow-up telephone call from a CHW to reassess breast cancer screening status. For example, participants will be asked if screening was performed within the last 120 days since the initial intervention, and if so, when it was performed, and when the participant plans to have their next routine breast cancer screening examination. The CHW also will re-administer portions of the HLK-BH program questions via the telephone and ask questions regarding breast cancer testing utilization, breast cancer screening barriers, perceived breast cancer susceptibility, screening self-efficacy, and breast cancer risk status and reassess Precaution Adoption Process Model behavioral breast cancer screening stage. Program evaluation and satisfaction questions will also be asked of each participant near the end of this final assessment. By re-administering portions of the HLK-BH program questions at the 120-day post randomization follow-up, the research team will be able to evaluate the differential impact of the **MI**^**2 **^intervention compared to the **C **intervention on the primary (e.g., breast cancer screening utilization) and secondary outcomes (e.g., breast cancer screening barriers and progression through the PAPM stages). Refer to Figure 2 for an overview of the flow of research participants.

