##### Aim #1

To compare the 120-day post randomization mammography screening completion rates of individuals who receive a computerized mammography "implementation intentions" (**MI**^**2**^) intervention, versus a comparison computerized condition of general breast cancer prevention health education (**C**).

For this aim, both the outcome (120-day post randomization breast cancer screening completion) and predictor (treatment group) are dichotomous, so a 2 × 2 table will be generated to compare the proportions of those completing screening between the **MI**^**2 **^versus **C **intervention groups. A χ^2 ^statistic will be used to test the null hypothesis of no difference in these proportions between these two [67]. The distribution of measured and unmeasured confounding variables (beyond community location) should be relatively balanced between the intervention groups due to the random assignment of the intervention within communities and participants. However, if serious imbalances are apparent from the descriptive statistics described above, we will use unconditional logistic regression to model this dichotomous outcome. Predictor variables will include the intervention group and the unbalanced demographic characteristics to reduce the impact of such biases. Indicator variables identifying the community will also be included to control for this stratification variable as described by Agresti [67]. The results of this logistic regression will be transformed into estimates of the proportion screened [68] adjusted for the potential confounding variables. The fit of the model will be assessed using the Deviance statistic and the Hosmer-Lemeshow goodness-of-fit test [68].

To measure the impact of attrition on the part of the study participant, a sensitivity analysis will be performed. This can be done using the methods described by Rothman and Greenland [69] by examining what the results would be under various assumed scenarios for those missing the outcome. This will include a conservative imputation approach which will assume that all of those for whom this outcome is unknown were not screened during the 120-day post randomization period.

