#### Sample Size and Sample Size Justification

This study will utilize Latina and AI/AN female participants from two distinct communities with approximately 121 randomized participants per community to test the main effects of the **MI**^**2 **^vs. **C **arms at 120 days post randomization. For this study, a total of 290 subjects will be randomized to either the **MI**^**2 **^or **C **treatment arms (to account for a possible 20% attrition rate from randomization to 120 day follow up). It is anticipated that 30% of those in the **MI**^**2 **^group will receive their breast cancer screening within the 120 day study period compared to 15% in the **C **group. A total of 242 subjects (121 per study arm) would have 80% power to detect the anticipated difference in screening rate between the **MI**^**2 **^and **C **groups at the α = 0.05 (two-sided) type I error rate (Table 5). Assuming up to a 20% attrition rate based on the research team's prior studies in rural Kansas, a total of 290 subjects will be randomized to either the **MI**^**2 **^or **C **treatment arms (145 per treatment). Additional screening rates were examined for study power (Table 5) to select an adequate sample size to detect clinically relevant differences. Numbers contained in Table 5 demonstrate that the sample will have at least 80% power to detect clinically relevant differences. Similar tables to Table 5 were also compared with varying sample sizes, with the final sample size selected being the choice that optimized both study power with the logistical constraints.

**Table 5 T5:** Power estimates (%) for a sample size of 121 subjects per group with α = 0.05 (two-sided)

		Breast Cancer Screening - Implementation Intentions	
		25%	30%
Breast Cancer Screening	10%	87	97
		
Controls	15%	Not Relevant	80

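### Table 2 lists answering the 120-day call as an inclusion criterion, a post-randomisation event that the rest of the protocol contradicts

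*Protocol article*

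**What the plan says.** All places are in the protocol article.

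- **Participant Eligibility, Table 2**, inclusion column: "Responded to 120-day post randomization follow-up call". The table lists home address and working telephone as a separate item.
- **Participant Eligibility, text above Table 2**: women need a current mailing address and "access to a functioning telephone to ensure that the 120 day telephone follow up can be completed". Response to the call is not required.
- **MI2 Intervention**: once a woman is found eligible, "the computer program will automatically and immediately assign them to either the intervention or control arm". The Control Arm section says the same.
- **120-Day Post Randomization Follow-Up**: in both arms, "participants will receive a follow-up telephone call from a CHW to reassess breast cancer screening status". This call supplies the primary outcome, by self-report.
- **Data Analysis, Aim #1**: a χ² "statistic will be used to test the null hypothesis of no difference in these proportions between these two" groups. No analysis set is named there. Attrition is handled separately: "To measure the impact of attrition on the part of the study participant, a sensitivity analysis will be performed", under various scenarios. One of these is described as follows: "This will include a conservative imputation approach which will assume that all of those for whom this outcome is unknown were not screened".
- **Sample Size and Sample Size Justification**: 290 women are randomised, 145 per arm, "to account for a possible 20% attrition rate from randomization to 120 day follow up". The stated power is 80% with 121 per arm.

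**The concern.** An inclusion criterion has to be knowable before assignment. This one is not. If someone applies Table 2 as written, a randomised woman who does not answer the call was never eligible and leaves the trial population. Because the call is also where the primary outcome is collected, the criterion amounts to requiring that the outcome be observed. The trial would then compare responders only, its flow diagram could show no attrition, and the planned attrition analysis would have nobody in it.

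A second, smaller matter sits in the attrition paragraph. Counting every unknown outcome as not screened gives a low estimate of each arm's screening rate. That does not make it cautious about the difference between arms. When follow-up is unequal, it favours the arm that is followed up better.

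**Working it through.** **1. The plan's own figure.** Inputs from Sample Size and Sample Size Justification: 30% v 15%, two-sided α = 0.05, 80% power. With mean rate 0.225:

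n per arm = [1.960·√(2·0.225·0.775) + 0.842·√(0.30·0.70 + 0.15·0.85)]² / 0.15² = 120.5, rounded up to 121.

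Power at 121 per arm is 80.2%. The stated figure reproduces, and it is a figure for women with a known outcome.

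**2. What the line would remove.** At the stated 20% attrition, 0.20 × 290 = 58 women, or 29 per arm, would fail the Table 2 criterion after randomisation. That leaves 116 per arm.

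**3. The passages side by side.**

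| Place | Status of a randomised woman who does not answer |
|---|---|
| Table 2 | Not eligible |
| Text above Table 2 | Eligible, if she had an address and telephone at baseline |
| MI2 and Control Arm sections | Already assigned |
| 120-Day Follow-Up | A participant who is to be called |
| Aim #1, attrition paragraph | A participant with unknown outcome |
| Sample size section | Counted in the 290 and in the 20% attrition |

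Table 2 stands alone against the other five.

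**4. Missing = not screened and the difference between arms.** The observed rate is the true rate × the proportion followed up. With no true difference, an assumed 20% in both arms and assumed attrition of 15% (MI2) v 25% (C):

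0.20 × 0.85 = 17% v 0.20 × 0.75 = 15%.

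The 2-point difference in favour of MI2 comes from follow-up alone. With equal attrition no such difference arises.

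The scenario can also be a weak stress test. Take 116 responders per arm at about the planned rates, 35 v 17 screened (p = 0.005).
- All missing not screened: 35/145 v 17/145, p = 0.006, almost unchanged.
- All 29 missing controls screened and no missing MI2 women screened: 35/145 v 46/145, direction reversed, p = 0.15.

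The informative scenarios are those that differ by arm.

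**5. Does deleting the line remove non-response bias?** Assume 15% truly screened in both arms, 80% response in C whatever the outcome, and MI2 response of 95% among screened and 75% among unscreened women. None of these response rates is in the document.

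- Responders only: MI2 rate = 0.15·0.95 / (0.15·0.95 + 0.85·0.75) = 0.1425/0.780 = 18.3%, against 15.0% in C. The two-sided 5% test, summed exactly over two binomials, rejects about 10% of the time.
- All 145 per arm, missing = not screened: 0.15·0.95 = 14.25% v 0.15·0.80 = 12.0%. The test rejects about 8.8% of the time.

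The excess over 5% is present under both analyses. It comes from the assumed response pattern and not from the Table 2 line.

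**6. Power if all 290 are analysed with missing = not screened.** At 20% attrition in both arms the contrast is 0.30·0.80 = 24% v 0.15·0.80 = 12%. With 145 per arm, power is 76.1% by the formula in step 1 and 76.9% by exact summation.

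**The case against.** The strongest defence is that the line cannot operate. Eligibility is settled in the first part of the computer session from age and screening history, and assignment follows at once. Nothing in the analysis section removes non-responders as ineligible, and several sections treat them as participants. On this view the bullet is a stray entry, perhaps a garbled form of the requirement to be reachable by telephone. Much of this stands: the document does not establish that a responders-only trial is intended. But the reachability item is already a separate part of Table 2, so the bullet is not a restatement of it. A reader who applies the table literally would exclude women after randomisation.

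A reader might also infer that the line itself inflates the false-positive rate to 10% or more. The documents do not support that. The outcome comes from the same call, so a non-responder has no outcome whether or not the line exists, and the inflated rates rest on assumed response rates. The protocol reports no response that differs by arm or outcome. It is possible that MI2 women who kept their plan answer more readily, but this is conjecture. The documents describe the plan contract as printed and agreed to, not as signed.

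Finally, the attrition paragraph already promises various scenarios, so arm-specific ones fit within it, and their detail can be left to an analysis plan. That makes the wording of the imputation a secondary point. The word conservative is still inaccurate for the between-arm contrast.

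**Conclusion.** The contradiction is real and should be corrected. Table 2 states an eligibility rule that cannot be known at assignment and that five other places in the article contradict. Its literal effect, at the protocol's own 20% attrition, is to make about 58 of 290 randomised women ineligible after the fact and to leave no missing outcomes to study. This needs no assumption beyond that attrition figure.

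The point about the imputation label is also correct but smaller. The 17% v 15% example rests on an assumed 20% screening rate and assumed attrition of 15% v 25%; it shows the direction of the error, not its likely size here.

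The false-positive rates of about 10% and 8.8% illustrate outcome-related non-response under assumed rates. They are not a consequence of the Table 2 line, and neither deleting it nor imputing not screened removes them.

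**What to change.** 1. Delete the follow-up response item from the inclusion column of Table 2. Keep the address and telephone item, which can be checked at baseline.
2. State that all 290 randomised women belong to the trial population in their assigned arm, and that women not reached at 120 days are counted and reported, by arm, as missing the primary outcome.
3. In the Aim #1 attrition paragraph, do not describe missing = not screened as conservative for the difference between arms. Let the scenarios already planned vary the non-responders' screening rate separately in MI2 and C.

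The cost is one deleted table line and a reworded paragraph; enrolment and data collection do not change. If missing = not screened were made the rule for the main comparison in all 290, the contrast would shrink to 24% v 12% and power to about 76-77%. That is a reason to choose the missing-outcome rule deliberately, since deleting the line does not settle it.
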